**ClinicalTrials.gov ID: NCT04936672**

## Study Identification

Unique Protocol ID: JKEUPM-2020-296

Brief Title: Effects of Brisk Walking Combined With Tai Chi Chuan on Health-Related Physical Fitness and Selected Health Parameters Among Older Chinese Women

[figure not shown] **NOTE** : Brief Title should have no more than 120 characters.

Official Title: Effects of Brisk Walking Combined With Tai Chi Chuan on Health-Related Physical Fitness and Selected Health Parameters Among Older Chinese Women

Secondary IDs:

## Study Status

Record Verification: September 2021

[figure not shown] **ERROR** : A record for an active study (Overall Recruitment Status is not Completed, Terminated or Withdrawn) must be reviewed, updated and verified at least once per year.

Overall Status: Active, not recruiting

Study Start: July 3, 2021 [Actual]

Primary Completion: October 23, 2021 [Anticipated]

[figure not shown] **ERROR** : Anticipated Primary Completion Date cannot be in the past.

Study Completion: October 24, 2021 [Anticipated]

[figure not shown] **ERROR** : Study Completion Date must be in the future for a study that is Active, not recruiting.

[figure not shown] **ERROR** : Anticipated Study Completion Date cannot be in the past.

## Oversight

U.S. FDA-regulated Drug: No

U.S. FDA-regulated Device: No

U.S. FDA IND/IDE: No

Human Subjects Review: Board Status: Approved

Approval Number: JKEUPM-2020-296

Board Name: Universiti Putra Malaysia

Board Affiliation: Jawatankuasa Etika Universiti/UPM

[contact]

Email: [contact]

Address:

Secretariat of JKEUPM

Unit of Ethics Research (Level 5)

Office of the Deputy Vice Chancellor (Research & Innovation)

Universiti Putra Malaysia

Data Monitoring: No

FDA Regulated Intervention: No

## Study Description

**Brief Summary:** Aging is a problem that exists in many countries in the world. China has a large population base and a large number of elderly people. Paying attention to the health of the elderly is a problem that the Chinese government and society have been paying attention to. In order to improve the physical fitness of the elderly, the government encourages the elderly to do more exercise. However, the elderly do not exercise usually, and the way of exercise is relatively simple, which cannot meet the needs of comprehensive improvement of the elderly's physical fitness. For example, endurance, strength, flexibility, and balance are the most important to the elderly's physical fitness. Tai Chi Chuan is very popular in China. 79.36% of people in China choose brisk walking as the basic exercise. These two exercises have no venue, equipment requirements, and relatively simple technical movements. They are more convenient for the elderly to implement, and according to the literature It is found that Tai Chi Chaun is very effective in improving the balance and flexibility of the elderly, while brisk walking is very effective in improving endurance, and both Tai Chi and brisk walking can improve the strength of the elderly. Therefore, the combination of Taijiquan and brisk walking in this study can meet the four exercise components of elderly people's comprehensive development of physical fitness, endurance, strength, flexibility, and balance, and through the literature, it is found that the effect of combined exercise is better than that of a single exercise. Therefore, this study is divided into 4 groups, Tai Chi Chuan group, brisk walking group, Tai Chi combination brisk walking group, and control group. The aim of this study is to evaluate the effectiveness of combine brisk walking and Tai Chi Chuan (BWTCC) on health-related physical fitness and selected health parameters among older Chinese women. The specific objectives of these studies are as follows:

1. To evaluate the effectiveness of brisk walking (BW), Tai Chi Chuan (TCC), and their combination (BWTCC) on health-related physical fitness (Cardiorespiratory fitness, Body composition, Flexibility, Muscular Strength, and Muscular endurance) among older Chinese women at pre-test, post-test and at three (3) months post-intervention.
2. To evaluate the effectiveness of brisk walking (BW), Tai Chi Chuan (TCC), and their combination (BWTCC) on health parameters (Blood pressure, Resting heart rate, Balance, Height, and weight) among older Chinese women at pre-test, post-test and at three (3) months post-intervention.

3. To evaluate the effectiveness of brisk walking (BW), Tai Chi Chuan (TCC), and their combination BWTCC on QoL among older Chinese women at pre-test and post-test.

The following hypothesis # HO1: There are no significant differences among the three intervention groups (BW, TCC and BWTCC) and with the control group on health-related physical fitness (Cardiorespiratory fitness, Body composition, Flexibility, Muscular Strength, and Muscular endurance) among older Chinese women at pre-test and post-test.

HO2: There are no significant differences among the three intervention groups (BW, TCC and BWTCC) and with the control group on health parameters (Blood pressure, Resting heart rate, Balance) among older Chinese women at pre-test and post-test.

HO3: There are no significant differences among the three intervention groups (BW, TCC and BWTCC) and with the control group on QoL among older Chinese women at pre-test and post-test.

[figure not shown] **NOTE : Brief Summary should have no more than 2500 characters.**

Detailed Description:

1. Quality assurance plan that addresses data validation and registry procedures Each group of sites that submit data to researchers has two personnel responsible for the quality of these data. The site coordinator has learned and fully understood all the agreements, policies, procedures, and definitions in the intervention process before the formal intervention process. All personnel involved in measuring and collecting data must learn systematic knowledge before the formal intervention, so as to ensure that all data are valid and accurate.
2. Data checks to compare data entered into the registry against predefined rules for range or consistency with other data fields in the registry.

Errors in data entry, transfer, or transformation accuracy: These occur when data are entered into the registry inaccurately. Avoidance or detection of accuracy errors can be achieved through upfront data quality checks (such as ranges and data validation checks), reentering samples of data to assess for accuracy (with the percent of data to be sampled depending on the study purpose), and rigorous attention to data cleaning.

Errors of intention: Avoidance or detection of intentional error can be challenging. Some approaches include checking for consistency of data between sites, assessing screening log information against other sources , and performing onsite audits (including monitoring of source records) either at random or “for cause.”

3. Source data verification to assess the accuracy, completeness, or representativeness of registry data by comparing the data to external data sources (for example, medical records, paper or electronic case report forms, or interactive voice response systems).

3.1. External audit of registration procedures The researcher will act as an external audit to ensure the quality level of the registry for a specific purpose, and these audits should be conducted according to pre-established standards. Pre-established criteria may include monitoring participant registration rates or sites that require attention from previous audit results, or monitoring may be based on on-site experience level, serious adverse event reporting rates, or identified issues. This approach can range from reviewing procedures and interviews with on-site personnel to checking and screening logs, to monitoring the process of recording the program.

3.2. Assurance of system integrity and safety All aspects of the data management process should follow a strict life cycle approach for system development and quality management. Each process is clearly defined and documented.

4. Data dictionary that contains detailed descriptions of each variable used by the registry, including the source of the variable, coding information is used (for example, World Health Organization Drug Dictionary, MedDRA), and normal ranges if relevant.

The variables involved here mainly include independent variables, dependent variables, independent variables include brisk walking, Tai Chi Chuan, and dependent variables include health-related physical fitness, health-related parameters, and quality of life.

The independent variable has no coding information, only the type of exercise, and the corresponding digital input information for the dependent variable.

4.1 Health-Related physical fitness Based on the index of ACSM's exercise for older adults. Health-Related includes Cardiorespiratory Fitness, Body Composition, Flexibility, Muscular Strength, and Muscular Endurance.

Cardiorespiratory Fitness is usually quantified by the maximum oxygen uptake (VO2max), which is a maximum capacity (exhaustive) test that lasts 5-15 minutes. VO2max, the maximum test has many ways, including bicycle, dynamometer, step, walking/jogging test. Generally speaking, these tests use sub-maximal exercise heart rate, age to predict maximum heart rate (usually 220-age), power estimation VO2max Submaximal tests are best to use the original plan, but it can be based on elderly subjects Exercise capacity or limiting factors are revised to suit the use (Simpson Jr., 2010).

Body composition measurement method can use simple measurement indicators such as height and weight [body mass index (BMI)], girth, waist-to-hip ratio and/or skinfold thickness, and only requires limited equipment; and Indicators, such as the use of underwater weighing, X-ray technology or ingestion of isotopes, require very high-end measuring equipment: the latter method is usually considered the "gold standard for body composition". For most trainers, limited equipment and easy operation are feasible (Rich, 2004b).

Flexibility tensility bendiness adaptability adjustability open-endedness openness to change changeability freedom latitude mobility variability fluidity versatility wriggle room wiggle room pliability suppleness pliancy malleability moldability stretchability workability limberness ductility plasticity elasticity stretch stretchiness whippiness springiness spring resilience give bounce bounciness willingness to compromise accommodation adaptability amenability cooperation tolerance forgivingness (Wojtek J. dhbdzko Zajko, 2017).

The definition of muscular strength is the maximal force that can be generated by a specific muscle or muscle group. Muscle strength is specific to the muscle group. type of contraction (static or dynamic; concentric or eccentric), the speed of the contraction, and the joint angle being tested (Rich, 2004b).

The definition of muscular endurance is the ability of a muscle group to execute repeated contractions over a period of time sufficient to cause muscular fatigue or to maintain a specific percentage of the maximum voluntary contraction for a prolonged period of time (Rich, 2004b).

**4.2 Health parameters** Health parameters are health-related impact indicators (Johar, 2012). In this study, resting heart rate, blood pressure, and balance were selected.

**Resting heart rate#RHR#** National Cancer Institute refers to in medicine, the number of times the heart beats within a certain time period, usually a minute. The heart rate can be felt at the wrist, side of the neck, back of the knees, top of the foot, groin, and other places in the body where an artery is close to the skin. The resting heart rate is normally between 60 and 100 beats a minute in a healthy adult who is at rest. Measuring the heart rate gives important information about a person's health. Also called a pulse.

Resting heart rate (RHR) is positively related to mortality. Regular exercise causes a reduction in RHR. Exercise—especially endurance training and yoga—decreases RHR. This effect may contribute to a reduction in all-cause mortality due to regular exercise or sports (Reimers et al., 2018).

**Blood pressure** National Cancer Institute refers to the force of circulating blood on the walls of the arteries. Blood pressure is taken using two measurements: systolic (measured when the heartbeats, when blood pressure is at its highest) and diastolic (measured between heartbeats, when blood pressure is at its lowest). Blood pressure is written with the systolic blood pressure first, followed by the diastolic blood pressure (for example 120/80).

Age and BMI showed as having the strongest direct effect on blood pressure. Age also had a direct effect on blood glucose level and blood cholesterol level. The effect of age on blood glucose and blood cholesterol was also mediated by BMI. Being of an older age had a direct effect on increased blood glucose, blood cholesterol, and blood pressure, while a higher BMI had a direct effect on increased blood pressure. As women get older, maintaining a normal BMI is beneficial to preventing the increase of their blood glucose, blood cholesterol, and blood pressure (Fikriana & Devy, 2018).

**Balance** Balance is the ability to maintain the body's line of gravity over its base of support. A correctly functioning balance system allows a person to maintain a proper vision while moving, to determine the direction and speed of movement, to identify the body's position in its space, and to make automatic postural adjustments to maintain posture and stability in varying circumstances (Boron & Boulpaep, 2016).

**4.3 Quality of Life** Quality of life (QOL) is defined by the World Health Organization as 'individuals' perception of their position in life in the context of the culture and value systems in which they live and in relation to their goals, expectations, standards, and concerns (Martin & Amin, 2017).

5. Standard Operating Procedures to address registry operations and analysis activities, such as patient recruitment, data collection, data management, data analysis, reporting for adverse events, and change management.

**5.1 Recruitment** **5.1.1 Recruit group** Group selection criteria# **Exclusion criteria:** classes participating in exercise Four classes were randomly selected by the university for the elderly, among which three classes were the brisk walking group, the Taichi Chuan group, the combination of Tai chi chuan and the brisk walking group, and the other one was the control group.

5.1.2 Screening participants The researcher selects the participants who meet the criteria by asking and asking participants to fill out the PAR-Q questionnaire.

The inclusion and exclusion criteria to screen and then check by the doctor. 5.2 Data collection I.Data collection will start after obtaining the ethical approval, and completed the initial 2-week pilot test.

II.Prior to data collection, the potential participants will be approached and screen for illegibility. Then, they will randomly be assigned into 4 groups; 3 experimental groups (Wk, TCC, TCC+ BW) and 1 control group by stratified sampling.

Cross groups contamination will be control by only selecting 2 clinics in one district. In total 4 districts will be randomly selected. Each district will be randomly assigned to either BW, TCC, TCC+ BW, or a control group. Besides, III.the participants in this study will also be advised not to share any information about their exercise content, time, and other information with their friends and peers.

IV.Four qualified instructors and 4 assistance instructors will be appointed to assist the 4 intervention groups. These instructors will be responsible for monitoring the intervention for the group assign to them. Twenty enumerators that hold a Bachelor's Degree in PE will be appointed to monitor and assist the subjects in each group.

V.All participants are required to accept the intervention at the same time, for example, it is necessary to specify the morning or afternoon of each intervention.

VI.Each experimental group selects 2 people to supervise and remind participants of their exercise status.

VII.1 person as a walking instructor with a national second-level sports social instructor qualification certificate, 1 person as a Tai Chi Chuan skill instructor with a third-level or higher qualification certificate for Tai Chi Chuan.

VIII.Participants in each group established a contact group and were reminded before each exercise. After the exercise, they were required to record a detailed exercise log, such as exercise time and exercise content.

IX.The process of instrument testing: Before the start of data collection, all instruments and documents required for testing will be checked to ensure the validity of the instrument during the test.

X.The test environment, test instruments, and test personnel are consistent. Test each test item 3 times, take the middle value.

XI.The data after the test are all checked and processed by two researchers. 5.3 Change Management A detailed manual of the process: If the international and reference standards change during the intervention, a detailed manual containing all registry strategies, processes, and protocols, as well as a complete data dictionary listing all data elements and their definitions, will be updated regularly. This is for researchers Data collection is crucial.

Infrastructure for continuous training: personnel changes are a common problem. Specific procedures and training infrastructure should be provided at all times to cope with any unexpected changes and replacements of registered personnel or providers who regularly enter data into the record office.

The method of notifying the change: through the mobile phone group, so that the participants can report the relevant data during the exercise to the recorder in time.

6. Sample size assessment

This was based on a four-group design and the assumption of detecting a moderate effect size (partial  $\eta^2 = 0.06$ ) for a given parameter, a moderate correlation of  $r = 0.5$  almost 1 repeated measures, a level of  $\alpha = 0.05$ , and power ( $1 - \beta$ ) of 0.8 (Timmons et al., 2018). This study will be conducted as a cluster-randomized trial (CRCT) with 4 groups and 20 people per group. The ICC value of 0.01 is used in the calculation of the design effect in this study (Killip et al., 2004). As such the design effect was calculated as below:

$$DE = 1 + \rho(m-1) \quad DE = 1 + 0.01(20-1) = 1.19$$

$$ESS = \text{effective sample size} = 80 * 1.19 = 96 \text{ (24 subjects per each group)}$$

According to the literature found in the highly relevant literature of this study, the final dropout rate was 5.75% (Guo LX., 2011). Considering this matter, the final sample size will be considered as 26 subjects per group and the total sample size of the study will be  $n = 104$ .

7. Plan for missing data to address situations where variables are reported as missing, unavailable, non-reported, uninterpretable, or considered missing because of data inconsistency or out-of-range results.
8. Statistical analysis plan The main methods of data collection in this study were statistical analysis and descriptive analysis.

Data will be analyzed using SPSS software (version 27, IBM Company, Chicago, IL, USA). Statistical significance will be reported at the 0.05 level. The data analysis will be preceded by data cleaning and assumption testing. Descriptive statistics will be used for all variables. Descriptive statistics will be reported as means and standard deviations (SD) or medians and interquartile range (IQR) for continuous variables (according to their distribution) and frequency and percentage for categorical variables. Two Way repeated measure ANOVA/ANCOVA or Generalized Estimating Equation (GEE) model for evaluation of the effectiveness of intervention programs on dependent variables will be used. Before the statistical analysis, assumptions underlying each statistical test will be checked and appropriate measures were taken when assumptions are violated.

[figure not shown] **NOTE :** Detailed Description should have no more than 12000 characters.

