## Study Design

Study Type: Interventional

Primary Purpose: Treatment

Study Phase: N/A

Interventional Study Model: Factorial Assignment

There are four groups, 1 control group, and 3 intervention groups. Three intervention groups include the brisk walking group, the Tai Chi Chuan group, and their combination group.

Number of Arms: 4

Masking: None (Open Label)

Try not to allow communication and contact between participants in each group. Researchers do not participate in training. Researchers do not disclose more research information. Data collection and entry should be operated by professional personnel.

Allocation: Randomized

Enrollment: 100 [Actual]

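### All test data are checked by two researchers in an unmasked trial, and no one who judges values inconsistent or uninterpretable is named as masked to arm; masking that step is cheap

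*Protocol*

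**What the plan says.** The relevant statements stand in several places in the protocol.

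- **Who checks.** Detailed Description, section 5.2 XI: "The data after the test are all checked and processed by two researchers".
- **Masking.** The Study Design section gives "Masking: None (Open Label" and names no masked role. It adds that "Researchers do not participate in training" and that professional personnel handle collection and entry.
- **What may become missing.** Detailed Description, item 7, covers values that are uninterpretable or "considered missing because of data inconsistency or out-of-range results". It does not say who decides.
- **Rules.** Item 2 has entries compared with predefined range and consistency rules, without giving limits.
- **Allocation.** Section 5.2 II assigns each of four districts to one arm. Section 5.1.1 instead describes four classes, one per arm.
- **Audit.** Section 3.1 is headed as an external audit of registration procedures and says "The researcher will act as an external audit to ensure the quality level of the registry for a specific purpose". It also says that "these audits should be conducted according to pre-established standards". Section 5.1.2 says "The researcher selects the participants who meet the criteria".
- **Monitoring.** The Oversight section records no data monitoring.

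**The concern.** Whether a result is uninterpretable or conflicts with another field is partly a judgement. If the person judging can see the arm, an odd value may be kept in one group and removed in another without anyone intending it. With 100 women enrolled in four arms (100 / 4 = 25 on average), a few such decisions carry some weight.

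This is a different matter from unmasked scoring of the tests. Scores taken by someone who knows the arm cannot be taken again, whereas the later handling of recorded values can be masked by holding back a few columns. The protocol does not use that opportunity, although it already has all test results pass through two named checkers.

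The audit label is a smaller problem. It claims an independence that the arrangement does not have, and a reader may give the data more credit than is due.

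**Working it through.** The plan gives no figure to reproduce, so the check is to set the passages side by side.

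1. **Is there discretion?** Yes, in part. Item 2 points to predefined rules, and a pure range check leaves little to judge once limits are set. Item 7 goes further and includes values that are uninterpretable or inconsistent with other data. A range limit does not settle these.

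2. **Is anyone who exercises it named as masked?** No. Section 5.2 XI gives checking and processing to two researchers. The Study Design section lists no masked role. Its separation of duties covers training, collection and entry, which are not the checking step.

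3. **Would removing the arm column be enough?** No. With one district per arm (section 5.2 II), the district name identifies the arm. With one class per arm (section 5.1.1), the class name does. Item 2 also contemplates comparing data between sites, so site labels could well be in use during checking.

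4. **Does the audit bear on outcome values?** No. On its scope, section 3.1 says "This approach can range from reviewing procedures and interviews with on-site personnel to checking and screening logs", and it mentions registration rates, site experience and adverse event reporting rates. It is a process audit. The only defect there is that the trial's own researcher is called external.

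**A bound, not an estimate.** Suppose someone with 25 per arm and no true effect deliberately deleted the lowest exercise value and the highest control value in every trial.

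- The expected minimum of 25 standard normal values is -1.965, so one deletion shifts a mean by 1.965 / 24 = 0.082 SD.
- Two deletions open a gap of 2 × 0.082 = 0.164 SD.
- In simulation, the two-sided error of a two-sample t-test rises from 5% to 10.7%. With the exercise-arm deletion alone it is about 6.5%.
- If the same one-sided deletion is confined to values beyond 3 SD (an assumed limit, since the protocol gives none), the gap is 0.009 SD and the error stays at about 5%.

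The first scenario is manipulation, and the last is closer to range checking. Neither measures this plan's bias. The contrast shows that the exposure lies in judgements outside the range rules.

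**The case against.** The strongest reply is that the protocol nowhere says values are set to missing with the arm in view. Item 7 names no decision-maker, and open-label status does not mean that the working file carries arm labels. The auditor, the screener and the two checkers are not said to be the same people. Predefined rules, audit standards, source data verification and professional data entry all limit free judgement. Cleaning limits, blind review and lock procedures commonly sit in an analysis or data management plan that is not shown.

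Much of this stands. A reader might infer that deletions are being made by people who see the arm, or that the so-called external audit is where this happens. The documents support neither reading: the first is not stated, and the audit covers registration procedures. Nor is the absence of numerical limits a finding, since they may be given elsewhere.

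What remains is narrower. The protocol itself assigns checking to two researchers, declares the trial unmasked, and lists no masked role. None of the mitigating text masks the checkers, and the rules do not decide what counts as uninterpretable.

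**Conclusion.** The point holds as a low-cost improvement to a stated procedure. In a trial with no masking, two researchers check and process all test data, some reasons for treating a value as missing need judgement, and no one making that judgement is named as masked to arm. Under either the district-level or the class-level description, the group label alone would disclose the arm.

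No size can be given for any resulting bias. The 10.7% error rate is a deliberate-manipulation bound and should not be quoted as the risk of this plan; under rule-bound range deletion the error stays near nominal. The conclusion rests on two readings: that checking takes place on a file from which the arm can be recognised, which the open-label design makes plausible but the text does not state, and that some judgement remains after the predefined rules are applied.

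The description of the audit as external is wrong as it stands, but this is a wording correction. It is not evidence about the handling of outcome values.

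**What to change.** Amend section 5.2 XI and the masking entry under Study Design so that:

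- range and consistency checks, set-to-missing decisions and outlier review are done on a file with neutral participant IDs and no arm, class or district names;
- coded group labels (for example A to D) are supplied only where between-site consistency or model-assumption checks need grouping;
- each decision is logged with its reason, the file is locked with a date, and the true arm is merged only afterwards.

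The exercise logs of section 5.2 VIII record what exercise was done, so they should stay out of that file. Someone other than the two checkers should hold the key.

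In section 3.1, call the audit internal. Having staff of one site audit another would not make it external or masked, because they too belong to an unmasked trial.

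The change needs no new staff. The downside is a short delay before results by arm are seen. Coded labels are also weaker than none, because a group may be guessed from its pattern, so they should be used sparingly. If checking is already complete, the report should say that it was not masked, if that is the case, and describe the audit as internal.

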## Outcome Measures

### Primary Outcome Measure:

1. Body composition measurement by Waist circumference

Measuring process: The measuring ruler should be a cocoa-curved but inelastic tape ruler. The ruler should be placed on the surface of the skin and should not be pressed against the subcutaneous fat tissue. If you use Gulick elastic handle, its handle can be extended to the same mark every time. The same part should be measured twice. If the difference between the two measurement results is more than 5mm, the scene should be measured again.

[Time Frame: 5 minutes]

2. Flexibility measurement by sit and reach test

The sit and reach test is a common measure of flexibility, and specifically measures the flexibility of the lower back and hamstring muscles. Seated forward bend test instrument to measure.

[Time Frame: 5 minutes]

3. Flexibility measurement by Back Scratch Test

The Back Scratch Test, or simply the Scratch Test, measures how close the hands can be brought together behind the back.

Use a meter to measure the overlapping part of your hands.

[Time Frame: 5 minutes]

4. Muscular strength measurement chair stand test

The chair stand test is similar to a squat test to measure leg strength, in which participants stand up repeatedly from a chair for 30 seconds.

The chair stand test is similar to a squat test to measure leg strength, in which participants stand up repeatedly from a chair for 30 seconds.

equipment required: a straight back or folding chair without arm rests (seat 17 inches/44 cm high), stopwatch

[Time Frame: 5 minutes]

5. Muscular strength measurement by Arm Curl test

The aim of this test is to do as many arm curls as possible in 30 seconds. equipment required: 4 pound weight (women, AAHPERD), 5 pound weight (women, SFT). A chair without armrests, stopwatch.

[Time Frame: 5 minutes]

6. Muscle endurance measurement by knee push-up

1. The push-up fitness test (also called the press-up test) measures upper body strength and endurance. Place the knees on the floor, the hands below the shoulders, and cross your feet.
2. Keeping your back straight, start bending the elbows until your chest is almost touching the floor.
3. Pause and push back to the starting position.
4. Repeat until the set is complete. No equipment. Scoring: Record the number of correctly completed push-ups.

[Time Frame: 5 minutes]

7. Muscle endurance measurement by Sit-up

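### Testing is open-label and no rule keeps the people who score the tests separate from the staff who monitor and assist each group, leaving effort-dependent primary outcomes open to avoidable tester bias

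*Protocol*

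**What the plan says.** The Study Design section gives the masking as "Masking: None (Open Label", with no masked role of any kind. The note beneath it adds that "Researchers do not participate in training" and that "Data collection and entry should be operated by professional personnel".

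Section 5.2 (Data collection), item IV, of the Detailed Description sets out two staff roles. On the instructors: "These instructors will be responsible for monitoring the intervention for the group assign to them". On the enumerators: "Twenty enumerators that hold a Bachelor's Degree in PE will be appointed to monitor and assist the subjects in each group".

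On testing itself, section 5.2, item X, states: "The test environment, test instruments, and test personnel are consistent. Test each test item 3 times, take the middle value". Item XI has two researchers check the data after the test. Section 1 of the Detailed Description (quality assurance) requires that "All personnel involved in measuring and collecting data must learn systematic knowledge before the formal intervention".

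The Primary Outcome Measure list has eight tests. For the knee push-up it gives a scoring rule: "Scoring: Record the number of correctly completed push-ups". The comparator is a no-intervention group that carries on with daily life.

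**The concern.** With exercise against no intervention, participants know what they are doing. The person holding the stopwatch or counting repetitions need not be someone who has worked with them. The protocol leaves this open: it masks nobody and does not bar a tester from having monitored, assisted or instructed the women tested.

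Stronger encouragement, or a more generous view of a valid repetition, at post-test in the exercise arms would add directly to the estimated exercise effect. The planned repeated-measures ANOVA/ANCOVA or GEE could not separate such a shift from a real effect, because it would follow the arm. What is at stake is the exercise-versus-control part of hypotheses HO1 and HO2.

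**Working it through.** The protocol gives no figure for this point, so the main check sets the text side by side. The arithmetic after it is illustration.

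**1. Does any rule separate or mask the testers?**

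| Provision | Where | What it does | Hides the arm, or separates tester from group? |
|---|---|---|---|
| Masking entry | Study Design | No masking | No |
| Researchers kept out of training | Study Design | Covers researchers only | Not for enumerators or instructors |
| Professional personnel collect data | Study Design | Sets a qualification | No |
| Prior training of measurers | Detailed Description, 1 | Reduces error | No |
| Consistent test personnel | 5.2, X | Standardises; could mean one team for all groups or one tester per group | Not stated |
| Middle of three readings | 5.2, X | Reduces noise | No: the median of three lenient counts is still lenient |
| Check by two researchers | 5.2, XI | Checks data after the test | No: cannot detect a generous count |
| Participants asked not to share exercise details | 5.2, III | Concerns friends and peers | Not directed at testers |

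None of these masks the tester or clearly separates testers from group staff.

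**2. Which outcomes are exposed?**

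- Effort-dependent counts or distance: chair stand, arm curl, knee push-up, sit-up and six-minute walk, that is 5 of 8 primary outcomes. The push-up rule also requires a judgement of correctness.
- Less exposed: waist circumference, sit and reach, and back scratch, which are tape or instrument readings (3 of 8).
- The Tinetti balance score is a rating, but it is a secondary outcome.

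**3. Illustration of size.**

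Inputs from the protocol: 100 enrolled (25 per arm if equal), significance level 0.05, correlation 0.5 between repeated measures, partial η² = 0.06. Assumptions: a two-sided test, no true effect, and a scoring shift of b SD equal in all three exercise arms and absent in control. The protocol gives no value for b.

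- SD of change = SD × √(2(1 − 0.5)) = 1 SD.
- Exercise (75) versus control (25): standard error = √(1/75 + 1/25) = 0.231 SD. At b = 0.2 the noncentrality is 0.2/0.231 = 0.866; with 98 df the rejection rate is 13.8%. At b = 0.3 it is 0.3/0.231 = 1.299, giving 25.1%.
- Four-group F test (3, 96 df): noncentrality = 100 × b² × 3/16. At b = 0.2 this is 0.75, giving 9.6%; at b = 0.3 it is 1.69, giving 16.2%.
- One exercise arm versus control (25 v 25), normal approximation: standard error = √(2/25) = 0.283 SD. Rejection is about 11% at b = 0.2 and about 19% at b = 0.3.
- Scale: f = √(0.06/0.94) = 0.253. If the three exercise arms are equal, the difference from control is 0.253/√(3/16) = 0.58 SD, so 0.2 SD is about a third of it (0.2/0.58 = 0.34). This treats η² as a between-group effect, and the protocol does not say which model term was sized.

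These rates ignore clustering. With one cluster of 25 per arm and the protocol's ICC of 0.01 applied to the analysed score, the variance of an arm mean grows by 1 + 24 × 0.01 = 1.24. The rates with no leniency at all are then already about 8% (75 v 25) and 10% (F test). At b = 0.2 they are about 17% and 15%.

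**The case against.** The strongest objection is that the mechanism is inferred. A reader might conclude that the enumerators who spend twelve weeks with a group also score its tests. The text does not say so: it gives enumerators the task of monitoring and assisting, and gives data collection to professional personnel. This stands. What can be said is that overlap is not excluded.

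A reader might also take consistent test personnel to mean the same tester following the same group from visit to visit. The wording can equally mean one team for all groups, which would be a safeguard. It cannot be counted for either side.

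Third, enumerators are appointed to each group, possibly including control, so familiarity with the tester may not differ by arm. The direction of bias then rests on staff expectations. It is plausible but not shown. If the shift were equal across the three exercise arms, comparisons among them, which are also part of the hypotheses, would be unaffected.

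Fourth, the illustration has no sourced input for the shift, its 5% baseline ignores clustering, and 75 versus 25 is not a contrast that the protocol names. All of this stands, so the figures show sensitivity and do not estimate a bias.

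Finally, the study started in July 2021 and is listed as active, not recruiting, so the pre-tests are probably done. Allocation is by class or district (5.1.1 and 5.2 differ), so a tester visiting a site may learn the arm. This limits the remedy but leaves the separation of testers from group staff feasible.

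**Conclusion.** The point holds as a correctable design weakness. The protocol chooses no masking, has no rule making testers independent of the group they test, and relies on five effort-dependent tests among eight primary outcomes. The training, median-of-three and data-checking rules reduce random error but do not address a shift that follows the arm.

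The documents do not support saying that enumerators do score the tests, that the results are biased, or that the bias has any particular size. The rise from 5% to about 14% holds only under the assumed 0.2 SD shift in every exercise arm, none in control, 25 per arm, a correlation of 0.5 and no clustering. The change should be made because it is cheap and the exposure is avoidable.

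**What to change.** In section 5.2, state for all tests still to be done (post-test and three-month follow-up) that:

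- testers are drawn from the existing twenty enumerators and did not monitor, assist or instruct the women they test;
- each tester tests women from all four groups where feasible, and is not told the arm;
- participants are asked not to disclose their group to the tester;
- a fixed encouragement script is used for the timed and counted tests.

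Update the masking entry only for assessments that were actually masked. Relabelling the whole trial as assessor-masked would misdescribe tests done before the change. For tests already completed, record who tested whom and report this as a limitation. If no tests remain, this reporting step is all that can be done.

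The cost is scheduling or travel between sites on test days. Some unmasking will remain because whole classes or districts share an arm. No extra staff are needed.
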